### Study groups

#### Control

As determined by the hospitals, participants in the control group will receive usual discharge education from their doctors and other healthcare professionals, such as nurses or pharmacists. This discharge education is usually delivered by a Chinese-speaking health professional or through an English-speaking family member and provides information that summarises discharge, medications and follow-up care, such as cardiac rehabilitation. At the conclusion of the study, control participants will receive a link to download the app.

#### Intervention

After baseline assessment and randomisation, a researcher who completes the baseline assessment will assist participants allocated to the intervention group with downloading and installing the app on their smartphone or tablet before hospital discharge. The researcher will ensure that the participants are familiar with the app and its functions and have access to it throughout the study period, in addition to their usual care. The participants will have unlimited independent access to all the educational modules. They will be encouraged to contact the researcher if they experience technical issues with the app during the study period.

### Intervention details

#### Intervention content

The education app, called ‘6 Steps to Cardiac Recovery’, for heart attack survivors was codesigned and developed in English.^29^ The app content includes six modules of evidence-based information recommended by international and Australian national guidelines for heart attack survivors and their families.^30^,^32^ The modules cover diagnosis/procedures, heart disease risk factors, cardiac rehabilitation, medications, heart attack warning signs and actions and ongoing medical review. Completing all six modules takes approximately 40 min. A virtual nurse, created using avatar technology, guides the user through the six modules and promotes engagement. Interactive questions, quizzes and games are used throughout the app to promote interest, and the virtual nurse provides instant responses based on the correctness of users’ responses.

#### Intervention co-adaptation process

The original app is likely less beneficial for patients from immigrant backgrounds who are not proficient in English and may have culturally specific needs. Therefore, this app was adapted to Chinese language and culture using a co-adaptation process with Chinese-speaking consumers. The process followed principles commonly used in cultural adaptation for psychosocial interventions to ensure that the content, context and delivery were tailored to the Chinese-speaking population.

Five steps were involved in co-adaptation, including (1) creating storyboards in Chinese; (2) storyboard review by consumers to ensure language and culture appropriateness; (3) developing an avatar-based prototype; (4) pretesting the prototype by Chinese-speaking consumers and (5) refining and retesting the app. Chinese-speaking patients (n=3) and bilingual clinicians (n=3) were substantially engaged in steps II and IV to ensure language accuracy, readability, understandability, clarity and cultural sensitivity (figure 2).

**Figure 2 F2:**
[figure not shown]
Co-adaptation process of the virtual nurse-guided education app for Chinese-speaking patients.

#### Intervention features

This simplified Chinese version of the app fully addresses Chinese-speaking patients’ language, culture, health literacy and technology literacy needs. Simple language and multiple visual methods are used to improve readability and understandability, and questions and games were incorporated to enhance engagement based on evidence.^33^ The virtual nurse’s Chinese name is Anxin (安欣), whose facial expressions were created using a Chinese model. Anxin interacts with users through natural and innate human communication modalities (facial expressions, body language, speech and natural language understanding), which are illustrated in the screenshots of the app (online supplemental images 1 and 2).

### Data collection and study outcomes

Assessments will occur at baseline and 1 and 3 months after hospital discharge through phone interviews conducted by a researcher, as listed in table 1.

**Table 1 T1:** Study outcomes and assessment time point

Study outcome	Measurement	Baseline	1 month	3 months
**Primary outcome**				
CHD knowledge	CADE-Q SV (Simplified Chinese)	✓	✓	✓
Knowledge, attitudes and beliefs about heart event	C-ACSRI	✓	✓	✓
**Key secondary outcomes**				
Self-management behaviours	CADSMS	✓		✓
Cardiac-related hospital admission	Self-reported or family reported		✓	✓
Healthcare service utilisation	Self-reported		✓	✓
**Other secondary outcomes**				
Cardiac-related mortality	Family reported		✓	✓
Quality of life	EQ-5D-5L	✓		✓
App acceptability	App user survey		✓	
App feasibility	Data analytics			✓
Barriers and facilitators of implementation	Individual interview and focus group			✓

C-ACSRI, Chinese version of Acute Coronary Syndrome Response Index; CADE-Q SV, short version of the Chinese-language Coronary Artery Disease Education Questionnaire; CADSMS, Coronary Artery Disease Self-Management behaviour Scale; CHD, coronary heart disease; EQ-5D-5L, Five-Level EuroQol five-dimension instrument.

The primary outcome will be the mean difference between intervention and control groups in CHD knowledge scores and knowledge, attitudes and beliefs about heart attack symptoms and responses. Key secondary outcomes will include CHD self-management behaviours, cardiac-related hospital admission and use of healthcare services. Other secondary outcomes will include cardiac-related mortality, quality of life, app acceptability, app feasibility and barriers and facilitators of implementation.

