**Methods and analysis:**

This multicentre, assessor-blinded, randomised controlled trial will recruit 98 Chinese-speaking inpatients following ACS with evaluation at 1 and 3 months postdischarge. Control participants in the control group will receive the usual ward-based patient discharge education. Intervention participants will additionally receive the education app installed on their devices before hospital discharge with unlimited access during the study period. Cultural relevance and linguistic accuracy for this Chinese version of an existing app were ensured through co-adaptation with Chinese-speaking consumers; the primary outcome will be coronary heart disease (CHD) knowledge, and secondary outcomes will include knowledge, attitudes and beliefs regarding heart attack symptoms and responses, CHD self-management behaviours, utilisation of healthcare services and quality of life. A process evaluation will be conducted alongside the trial to assess the acceptability and feasibility of the app. Between-group comparisons will be made using 95% CIs, accounting for baseline differences using linear mixed effects or mixed effects logistic regression models.

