#### Knowledge, attitudes and beliefs about heart attack symptoms and responses

Participants’ knowledge, attitudes and beliefs about heart attack symptoms and responses will be measured using the Chinese version of the ACS Response Index at 1 and 3 months posthospital discharge. The measure comprises three subdomains: heart attack knowledge, attitudes and beliefs. The 21-item knowledge subdomain is scored based on dichotomous responses (yes/no) to a statement, with each correct response receiving 1 point, for a maximum score of 21. The 5-item attitudes subdomain is scored on a 4-point Likert scale, ranging from ‘not at all’ (1 point) to ‘very sure’ (4 points), for a maximum score of 20. The 7-item beliefs subdomain is scored on a 4-point Likert scale, ranging from ‘strongly agree’ (1 point) to ‘strongly disagree’ (4 points), for a maximum score of 28. The questionnaire has been translated and validated in Chinese patients with cardiac conditions.^35^

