### Statistical analysis

Statistical analysis will follow the intention-to-treat principle and a prespecified statistical analysis plan led by a blinded statistician. Descriptive statistics will be used to characterise participants. The analysis of variance (ANOVA) will be used to compare the primary outcome and estimate the mean difference and 95% CI. Furthermore, to assess whether there is a change in the outcome over time (baseline, 1 month and 3 months) within and between groups, a linear mixed effects regression model will be used with a random intercept for patients to account for individual variability. Assumptions for ANOVA and the linear mixed-effects model will be assessed prior to analysis. For ANOVA, independence, normality within groups and homogeneity of variances will be checked using Levene’s test, and outliers will be addressed if necessary. For the mixed-effects model, linearity, residual normality and homoscedasticity will be evaluated through diagnostic plots. If assumptions are violated, corrective measures such as data transformation or robust methods will be applied. In the case of missing data that are missing at random in nature, multiple imputations will be used. For secondary continuous outcomes, linear mixed effects regressions will be performed to assess whether there is change in the outcomes over time within and between groups. Similarly, for secondary categorical outcomes, mixed effects logistic regression models will be used to test for the change in the outcomes over time within and between groups.

Interview audio files will be transcribed verbatim into simplified Chinese and then translated into English by a bilingual researcher. To ensure the accuracy and reliability of the translation, another bilingual author will randomly audit five translated transcripts and back-translate these from English into simplified Chinese. The data will then be analysed using directed content analysis, with coding and theme generation facilitated by an Excel spreadsheet.

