### Sample size calculation

Since there is no established minimally important difference in disease knowledge or similar intervention for the CADE-Q SV (Simplified Chinese), the sample size calculation is based on a mean change of 2.3 points (SD 3.6), which has been published in patients with CHD precompleting and postcompleting a comprehensive cardiac education programme.^41^ A total of 78 participants (39 per group) will be required to detect a between-group difference in CADE-Q SV (Simplified Chinese) score of 2.3 points with (α=0.05, 80% power) (calculated from https://sample-size.net/sample-size-means/). Accounting for a 20% dropout rate, 98 patients (49 per group) will be needed.

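### The article contradicts itself on the primary outcome: the C-ACSRI is secondary in the abstract but primary in Table 1 and the outcomes text, while the sample size covers the CADE-Q SV only

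*Protocol article*

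**What the plan says.** The protocol article gives the C-ACSRI (Chinese version of the ACS Response Index) two different ranks.

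- **Abstract, Methods and analysis:** "the primary outcome will be coronary heart disease (CHD) knowledge", while "secondary outcomes will include knowledge, attitudes and beliefs regarding heart attack symptoms and responses".
- **Table 1:** the block headed Primary outcome has two rows: CHD knowledge (CADE-Q SV) and "Knowledge, attitudes and beliefs about heart event" (C-ACSRI).
- **Outcomes paragraph below Table 1:** the primary outcome is the "mean difference between intervention and control groups in CHD knowledge scores and knowledge, attitudes and beliefs about heart attack symptoms and responses".

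Three other sections bear on which version the design was built for.

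- **Statistical analysis:** "The analysis of variance (ANOVA) will be used to compare the primary outcome and estimate the mean difference and 95% CI". The primary outcome is in the singular.
- **Sample size calculation:** 78 participants (39 per group) are required "to detect a between-group difference in CADE-Q SV (Simplified Chinese) score of 2.3 points" at α=0.05 and 80% power, raised to 98 for 20% dropout. No effect size, SD or power is given for the C-ACSRI.
- **Description of the C-ACSRI:** "The measure comprises three subdomains: heart attack knowledge, attitudes and beliefs", with maxima of 21, 20 and 28. No total is described. The CADE-Q SV, by contrast, has an overall score with a maximum of 20.

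**The concern.** The primary outcome decides what the trial may claim. Here one instrument is primary in two places and secondary in a third, all in current text. If the CADE-Q SV shows no difference and a C-ACSRI score does, Table 1 would support reporting success on a primary outcome, and the abstract would support reporting that the primary outcome was not met. Both could be called prespecified.

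The design figures also belong to one version only. The error rate and power in the sample size calculation describe a trial with a single primary outcome, the CADE-Q SV. If the C-ACSRI is also primary, at least one of those figures no longer describes the trial. Which one depends on whether success on either instrument is enough or both are needed, and the article does not say.

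**Working it through.** **Inputs.** From Sample size calculation: difference 2.3, SD 3.6, α=0.05 (two-sided reproduces the stated N), power 80%, 39 per group, dropout 20%. Assumed, because the article gives no figure: the correlation between scores and, for joint power only, the standardised effect on the C-ACSRI. Each score is tested once, at one time point.

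**1. The plan's own figure.** n per group = 2(z₀.₉₇₅ + z₀.₈₀)² × SD² / difference² = 2 × (1.960 + 0.842)² × 3.6² / 2.3² = 38.5, rounded up to 39, or 78 in total. With dropout, 39 / 0.8 = 48.75, rounded up to 49 per group, or 98. The stated figures reproduce for one test at the full 0.05 on one instrument. A t-test calculation gives 40 per group, and power at 39 per group is 80.5% (normal) or 79.5% (t).

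**2. If either instrument suffices, each at 0.05.** For m independent scores the family-wise error is 1 − 0.95^m. For correlated scores it is the probability that at least one of m equicorrelated normal statistics exceeds 1.96 in absolute value.

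| Scores tested | Correlation 0 | 0.5 | 0.8 |
|---|---|---|---|
| 2 (CADE-Q SV and one C-ACSRI score) | 9.8% | 9.1% | 7.8% |
| 4 (CADE-Q SV and three C-ACSRI subdomains) | 18.5% | 15.6% | 11.4% |

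**3. If either suffices and alpha is split evenly.** Power for the CADE-Q SV at 39 per group (t-test) falls from 79.5% to 70.3% at 0.025 (two scores) and 60.5% at 0.0125 (four scores). By the normal formula used for the stated N, 80% power at 0.025 needs 47 per group; 47 / 0.8 = 58.75, so 59 per group, or 118 in total.

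**4. If both instruments must succeed.** No alpha split is needed. Suppose the C-ACSRI had one score with the same standardised effect as the CADE-Q SV, 2.3 / 3.6 = 0.64. Joint power at 39 per group is then 0.795² = 63% at correlation 0 (t-test), about 69% at 0.5 and 74% at 0.8 (normal approximation). With a smaller C-ACSRI effect it would be lower.

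**5. If the CADE-Q SV is the sole primary.** Alpha 0.05, 80% power and N = 98 all stand as written.

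Only case 5 agrees with the abstract, the singular wording of the analysis section and the sample size calculation together.

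**The case against.** The strongest defence is that the article condenses a fuller plan. The Statistical analysis section refers to a prespecified statistical analysis plan, which is not shown. Success rules, multiplicity control and the scoring of the C-ACSRI are commonly left to such a plan. That stands, and three stronger readings fall with it.

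- A reader might infer that the trial has no alpha control. The article is silent on it, but silence there does not show absence from the analysis plan.
- A reader might infer four primary scores. The article names two constructs and two instruments. It describes three C-ACSRI subdomains and no total, but nowhere says that each is tested as a primary. What can be said is that the C-ACSRI score to be analysed is not identified.
- A reader might infer that the 5% error rate is necessarily breached. That holds only if success on either instrument is enough. If both are required there is no inflation, and the cost is power.

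Nor would a null CADE-Q SV result with a positive C-ACSRI result be uninterpretable. Both could be reported with confidence intervals; what would be unclear is which result is confirmatory.

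The defence does not reach the contradiction itself. An analysis plan could settle the C-ACSRI's rank only by overruling either the abstract or Table 1 with the outcomes text. It would also leave the published sample size with no basis for a second primary outcome.

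**Conclusion.** The point holds as a contradiction in the current text. The abstract has one primary outcome; Table 1 and the outcomes paragraph have two. The singular wording of the analysis section and the sample size calculation fit the abstract. The sample-size arithmetic is correct; what is unsettled is which outcome or outcomes it serves.

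The size of the problem depends on a success rule that the article does not give. With either instrument sufficient at 0.05, the family-wise error is about 9.1% to 9.8% for two scores, and 15.6% to 18.5% if the three subdomains are tested separately, for assumed correlations of 0.5 to 0. With both required, alpha is kept but joint power is about 63% to 74% for correlations of 0 to 0.8, on the further assumption of an equal standardised effect. These figures show what each reading would imply; they are not established properties of the trial. The conflict should be corrected before unblinding, because it determines what the trial can conclude.

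**What to change.** State in the outcomes paragraph and in Table 1 that the CADE-Q SV total score is the sole primary outcome. Move the C-ACSRI to the key secondary outcomes, reported with 95% CIs. This matches the abstract, the analysis section and the sample size calculation, and N stays at 98.

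If both are to be kept in a confirmatory role, test the CADE-Q SV total first at 0.05. Only if that is significant, go on to the C-ACSRI, as one named score or as named subscales in a fixed order. The order matters: three unordered subscale tests at 0.05 in the second step would carry an error of 1 − 0.95³ = 14.3% if independent, or about 12.5% at correlation 0.5. Say that the 80% power applies to the CADE-Q SV only.

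Neither option needs more patients. The cost of the first is that the C-ACSRI loses primary status. Recruitment was planned to start on 1 July 2024, so this may be a change during the trial. Under Ethics and dissemination, modifications go to the ethics committee, investigators, participants and trial registry, and this should be done before unblinding. Whether the registry record or the analysis plan also needs changing cannot be judged from the article.

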#### Coronary heart disease knowledge

CHD knowledge will be measured using the short version of the Chinese-language Coronary Artery Disease Education Questionnaire (CADE-Q SV) at 1 and 3 months after hospital discharge.^34^ This 20-item questionnaire assesses participants’ overall CHD knowledge and five subdomains related to disease, risk factors, exercise, nutrition and psychological aspects, with four items in each subdomain. Each item is scored based on a ‘true’, ‘false’ or “I don’t know” response. Each correct answer receives 1 point for a maximum score of 20 for overall knowledge and 4 points for each domain. The CADE-Q SV has been validated among Chinese immigrants with CHD.^34^

#### Knowledge, attitudes and beliefs about heart attack symptoms and responses

Participants’ knowledge, attitudes and beliefs about heart attack symptoms and responses will be measured using the Chinese version of the ACS Response Index at 1 and 3 months posthospital discharge. The measure comprises three subdomains: heart attack knowledge, attitudes and beliefs. The 21-item knowledge subdomain is scored based on dichotomous responses (yes/no) to a statement, with each correct response receiving 1 point, for a maximum score of 21. The 5-item attitudes subdomain is scored on a 4-point Likert scale, ranging from ‘not at all’ (1 point) to ‘very sure’ (4 points), for a maximum score of 20. The 7-item beliefs subdomain is scored on a 4-point Likert scale, ranging from ‘strongly agree’ (1 point) to ‘strongly disagree’ (4 points), for a maximum score of 28. The questionnaire has been translated and validated in Chinese patients with cardiac conditions.^35^

#### Self-management behaviours

Participants’ CHD self-management behaviours will be measured 3 months posthospital discharge using the Coronary Artery Disease Self-Management behaviour Scale. This 27-item questionnaire has three subdomains, including emotional self-management behaviours, daily life self-management behaviours and medical self-management behaviours. Participants rate each item on a 5-point Likert scale, for a total score ranging from 27 to 135, with a higher score indicating better self-management behaviours. The questionnaire was originally developed and validated in Chinese patients with CHD.^36^

#### Cardiac-related hospital admission

Cardiac-related hospital admission will be collected from participants’ self-reported data and cross-referenced with electronic medical records.

#### Healthcare service utilisation

Healthcare use, including cardiac rehabilitation attendance and other healthcare services (regular planned and/or unplanned visits to their general practitioners, a chronic disease management plan, enrolment in a health coaching service and weight loss programmes), will be collected from participants’ self-reported data and cross-referenced with electronic medical records.

#### Cardiac-related mortality

Cardiac-related mortality will be based on family reported data and cross-referenced with hospital electronic medical records.

#### Quality of life

Quality of life will be measured 3 months posthospital discharge using the Five-Level EuroQol five-dimension instrument (EQ-5D-5L) (Simplified Chinese).^37^ Participants will be assessed across five health dimensions, including mobility, self-care, usual activities, pain/discomfort and anxiety/depression, based on five response categories from level 1 to 5 corresponding with no problem, slight problems, moderate problems, severe problems and extreme problems, respectively.^38^ Alongside the five health dimensions, the EQ visual analogue scale will be used to assess participants’ ‘own health today’ with end points labelled ‘best imaginable health state’ (100) and ‘worst imaginable health state’ (0). The EQ-5D-5L has been validated in Chinese populations.^37^

#### Process outcomes and measures

Alongside the clinical trial, a process evaluation will be conducted to explore the acceptability, feasibility and barriers/enablers to implementing the education app from participants’ perspectives. The process evaluation will be guided by the Exploration, Preparation, Implementation and Sustainment Framework.^39^

#### App acceptability

Intervention participants will be invited to complete a user satisfaction survey after 1 month, based on previous digital health intervention trials.^29 40^ This 34-item questionnaire comprises categorical, multiple-choice and open-ended questions to explore participants’ perceptions of the app content, visuals/audio, nurse character, understandability, usefulness and functionality.

#### App feasibility

Field notes on app feasibility will be taken during recruitment. Quantitative data will also be collected to determine app feasibility, which will include (1) uptake of the intervention (% of eligible participants who enrolled in the study, noting any difficulties in enrolling and providing the app to participants on the hospital ward), (2) retention (% of enrolled participants assessed at 3-month follow-up) and (3) compliance with the intervention (% of participants who completed all six modules in the app and Google data analytics, such as time spent on each module, frequency of access to each module).

